Having demonstrated the potential clinical benefit of CARA through reduction in doses to organs at risk (OARs) [26], the current study is designed to assess the effectiveness of utilizing CARA V3.0 to reduce the incidence of acute skin reactions in the IMF in patients at high risk of MD undergoing breast RT. In this protocol, the IMF refers to the areas of skin on the inferior breast surface and on the chest that are in contact when the breast is unsupported in the supine position. The IMF is effectively eliminated when using CARA, but skin reactions are being monitored on this skin area after removal of the breast support, post-RT delivery. Compared to the pilot phase II trial, this is a phase III randomized controlled trial (RCT) on a larger population that incorporates improvements from the pilot and the use of PROs for the primary outcome measure. In addition, a discussion of the clinical acceptability of CARA, with respect to workflow measures, setup reproducibility, and therapist satisfaction, will be provided.

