#### Treatment planning and dose constraints

Treatment planning will be performed for both study arms according to current standard of care using the Varian Eclipse AAA algorithm (V13.6) or equivalent, as assessed at credentialing or during the trial if system upgrades occur. Correction for lung inhomogeneity will be used.

PTV, OTV or Breast_Eval coverage by the 95% isodose surface is required. The dose homogeneity objective is V105% < 2% of the OTV. Beam energy may be adjusted as required to achieve PTV coverage and homogeneity criteria, however PTV coverage will take priority over dose homogeneity if the latter cannot be met. For treatments of 15, 16, 25, or 28 fractions, ipsilateral lung V20 Gy shall be ≤ 15% of the lung volume (≤ 35% if regional nodes are treated) and V25 Gy heart shall be ≤ 5% of the heart volume. For 26 Gy in 5 fraction treatments, ipsilateral lung V8 Gy shall be ≤ 15% of the ipsilateral lung volume, heart V1.5 Gy shall be ≤ 30% and heart V7 Gy shall be ≤ 5% of the heart volume. Sliding window or field-in-field (step and shoot) IMRT may be used as available at the treating center.

All treatment plans in this study will be approved by the treating oncologists and designated physicists at each site, including a quality assurance check on all contours. All constraint violations will be noted on the planning data form.

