### Statistics and analysis

#### Sample size calculation and recruitment period

Based on evidence from previous studies [5–8], we expect a control arm rate of 50% for any degree of MD in the IMF. Due to a reduction in skin folds and reduction in V105% with reduced breast separation, we hypothesize a rate of 30% moist desquamation in the study arm (i.e., an absolute decrease in incidence of 20%). For this effect size with 80% power and two-tailed α = 0.05, the sample size is 93 patients in each arm. Because of the nature of the study and 10% observed loss to follow-up in our pilot study, we will enroll 110 patients in each arm.

We expect that a 3-year recruitment period will be sufficient for the trial. A similar multicentre study from our team [5] achieved a similar recruitment rate in the same patient population drawing from only two centres.

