#### Randomization procedure and tracking

The random allocation lists will be computer-generated by a statistician not associated with the study. Randomization will use permuted blocks of random size. Stratification is by dose fractionation, by presence of IMF skin fold, and by centre.

The allocations will be uploaded into a password-protected website on secure hospital servers. When an eligible and consenting patient is identified in advance of their CT simulation appointment, the study coordinator or study radiation therapist will enter a patient identification code, and the computer will issue the allocation and a patient study number. An automated audit trail will track the patient identifier and study number, the treatment allocation, and the date, time, and site of the transaction.

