#### *Statistical methods – *primary* outcome*

The proportion of patients experiencing MD in the IMF in the two arms will be compared using logistic regression to assess the effect of treatment, adjusting for brassiere cup size, skin fold size, BMI, smoking status, and dose fractionation schedule. An unadjusted comparison will also be made using the chi-square test, or Fisher’s exact test, if appropriate. Those participants who do not complete all follow-up but have reported MD are included in the analysis. Those who do not complete all follow-up and do not report MD will be excluded from the primary analysis. A sensitivity analysis including those lost to follow-up will be done using multiple imputations for missing data.

Baseline descriptive variables (e.g., age, smoking status, BMI, as described in the section Baseline Assessment) will be compared descriptively between the two arms of the study and assessed for imbalance. Formal statistical comparisons of baseline characteristics in RCTs are not advised [35].

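### Women without an infra-mammary fold are eligible and form their own randomisation stratum, but the endpoint site is defined as a fold and the primary model fits one arm effect without that stratum, so the effect may be diluted by an unknown amount

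*Protocol article*

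**What the plan says.** **Eligibility.** The inclusion criteria accept either a skin fold of at least 0.5 cm or lateral breast tissue that falls behind the mid-axilla line, or both. Lateral ptosis alone is enough. The Patient population and Informed consent sections say the same.

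**Randomisation.** "Stratification is by dose fractionation, by presence of IMF skin fold, and by centre" (Randomization procedure and tracking). The trial therefore expects women without a fold.

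**Endpoint site.** The last paragraph of the Background defines the IMF as the "areas of skin on the inferior breast surface and on the chest that are in contact when the breast is unsupported". The Primary endpoint section scores moist desquamation (MD) in the IMF from a report of open skin located under the breast, unless a blinded assessor rules it out. Any woman can give that answer.

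**Sample size.** "we expect a control arm rate of 50% for any degree of MD in the IMF", and then: "Due to a reduction in skin folds and reduction in V105% with reduced breast separation, we hypothesize a rate of 30% moist desquamation". One contrast is applied to everyone.

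**Primary model.** Logistic regression for the effect of treatment, "adjusting for brassiere cup size, skin fold size, BMI, smoking status, and dose fractionation schedule". Fold size is in this list. The fold-presence stratum is not.

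**The concern.** Read literally, the endpoint site does not exist in one whole randomisation stratum, while the scoring rule still counts events there. The definition and the rule need to agree, because otherwise MD in the IMF means different things in the two strata.

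The single arm effect is the second difficulty. The device is meant to remove the fold and to reduce breast separation. A woman without a fold can gain only from the second route. If her gain is smaller, the pooled difference is smaller than the one the trial was sized for. A non-significant pooled result could then conceal a real benefit in women with a fold, and a significant one would say little about women without. The factor that separates the two cases is recorded before randomisation but does not appear in the stated model.

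**Working it through.** **Inputs from the article:** 50% versus 30%, two-sided α = 0.05, 80% power, 93 per arm, 10% loss, 110 enrolled per arm (Sample size calculation). **Assumed, because the article gives no value:** the no-fold share f, the control-arm MD rate b in women without a fold, and their absolute benefit e.

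**1. The stated sample size.** Pooled-variance formula for two proportions, no continuity correction:

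n = [1.96·√(2·0.40·0.60) + 0.8416·√(0.50·0.50 + 0.30·0.70)]² / 0.20² = [1.358 + 0.571]² / 0.04 = 93.0

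The stated 93 reproduces exactly. Allowing for loss, 93/0.9 gives 104, so 110 is sufficient. With 110 × 0.9 = 99 evaluable per arm, power is 82%.

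**2. Mixed population.** Women with a fold keep 50% versus 30%:

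- control: p_C = (1 − f)·0.50 + f·b
- device: p_E = (1 − f)·0.30 + f·(b − e)
- power = Φ{[(p_C − p_E)·√n − 1.96·√(2p̄(1 − p̄))] / √(p_C(1 − p_C) + p_E(1 − p_E))}, where p̄ is the mean of the two rates

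Example with f = 20%, b = 20%, e = 0: p_C = 0.44, p_E = 0.28, p̄ = 0.36. Power = Φ[(0.16 × 9.950 − 1.96 × 0.6788)/0.6693] = Φ(0.39) = 65%.

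For f = 20% and n = 99 per arm:

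| Women without a fold | p_C vs p_E | Pooled difference | Power |
|---|---|---|---|
| no benefit, b = 10% | 42% vs 26% | 16 points | 66% |
| no benefit, b = 20% | 44% vs 28% | 16 points | 65% |
| no benefit, b = 30% | 46% vs 30% | 16 points | 64% |
| 10-point benefit, b = 20% | 44% vs 26% | 18 points | 76% |
| 10-point benefit, b = 30% | 46% vs 28% | 18 points | 75% |
| same rates and effect as with a fold | 50% vs 30% | 20 points | 82% |

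Over other shares, with no benefit and b = 10–30%, power is 74–75% at f = 10%, 53–57% at 30% and 42–47% at 40%. With a 10-point benefit and b = 20–30%, it is 79% at f = 10% and 71–73% at 30%.

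**3. What adjustment can do.** Logistic models with a fold-presence term were simulated against the unadjusted test (2,000 runs, 99 per arm, no benefit without a fold, b = 20%). Power was 66% versus 65% at f = 20%, and 56% versus 54% at f = 30%. Adjustment is worth having but does not undo dilution.

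**4. What stratum estimates can show.** At f = 20% there are 0.8 × 99 = 79.2 women with a fold per arm and 19.8 without.

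- Fold present: testing 50% versus 30% at 79.2 per arm has 73% power. The 95% CI half-width is 1.96·√(0.46/79.2) = 15 points.
- Fold absent, 20% in both arms: half-width 1.96·√(0.32/19.8) = 25 points.
- Interaction on the risk-difference scale: SE = √(0.46/79.2 + 0.32/19.8) = 0.148. For a true gap of 20 points, power is Φ(0.20/0.148 − 1.96) = 27%. It is lower still if women without a fold gain something.

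**The case against.** The strongest reply is that the hypothesis does not rest on the fold alone. The sample-size section also credits lower V105% with reduced separation. The Background reports that both fell in the pilot, and the CT simulation section sets the device to correct lateral droop, the very feature that admits women without a fold. This stands: some benefit without a fold is part of the stated hypothesis.

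One might answer that both arms share a planning goal, "The dose homogeneity objective is V105% < 2% of the OTV", so V105% cannot differ. The documents do not support that. It is an objective that yields to target coverage, and lower V105% with the device is itself a secondary objective.

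Three further points also stand. The 50% rate appears in the Background as an upper figure for large or pendulous breasts in general, not only for women with a fold. Women without a fold are not structural non-events, because the questionnaire item applies to them. And subgroup estimates are commonly left to an analysis plan, so their absence from an article is not in itself a fault.

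What the reply leaves untouched is the conflict between the site definition, the eligibility rule and the scoring rule, and a stated covariate list that omits the fold-presence stratum. Fold size, presumably zero where no fold exists, covers part of that stratum, but a size term need not capture a step between absence and presence.

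**Conclusion.** The point holds as a matter of reconciliation and analysis specification. The endpoint site as defined does not fit all eligible women, and the stated model summarises with one effect two strata in which the device can work by different routes.

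The size of any dilution cannot be fixed from the article. At an assumed 20% share, power ranges from 64–66% with no benefit in women without a fold, through 75–76% with a 10-point benefit, to 82% with the same rates and effect. It is a minor matter if the share is near 10%, and a serious one only if the share is 20% or more and these women gain little.

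A reader might infer that the stated power is wrong. It is not: 93 per arm reproduces exactly, and 80% is correct if one contrast holds regardless of fold. A reader might also infer that the conclusion should be confined to women with a fold, or that the fold-present estimate is the true test of the hypothesis. Neither follows. The objective covers women with large or pendulous breasts. About 20 women per arm without a fold would rarely settle the matter, so such a rule would restrict the claim almost by default. A second confirmatory test would also need its own share of α.

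**What to change.** - **Statistical methods – primary outcome:** keep the pooled analysis of the whole trial population as primary. Add the fold-presence stratum to the model. Pre-specify the arm effect with 95% CI in the fold-present and fold-absent strata, with an arm-by-fold interaction term, as supportive estimates that carry no separate confirmatory claim.
- **Background definition, Primary endpoint and Inclusion criteria:** reconcile them, so that in women without skin contact the endpoint site is the skin under the breast.
- **Sample size calculation:** state that the 80% power assumes the same 50% to 30% contrast whether or not a fold is present.

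The cost is wording only. Fold presence is already recorded for randomisation, so no patients, data or procedures are added. The added model term gains a little power where MD rates differ by fold. The drawback is that the fold-absent estimate and the interaction test will be imprecise and should be presented as such.

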#### *Statistical methods – *primary* outcome*

The proportion of patients experiencing MD in the IMF in the two arms will be compared using logistic regression to assess the effect of treatment, adjusting for brassiere cup size, skin fold size, BMI, smoking status, and dose fractionation schedule. An unadjusted comparison will also be made using the chi-square test, or Fisher’s exact test, if appropriate. Those participants who do not complete all follow-up but have reported MD are included in the analysis. Those who do not complete all follow-up and do not report MD will be excluded from the primary analysis. A sensitivity analysis including those lost to follow-up will be done using multiple imputations for missing data.

Baseline descriptive variables (e.g., age, smoking status, BMI, as described in the section Baseline Assessment) will be compared descriptively between the two arms of the study and assessed for imbalance. Formal statistical comparisons of baseline characteristics in RCTs are not advised [35].

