#### CT simulation

CT simulation will be performed with the patient in supine position for both study arms. The preferred patient position is both arms above the head with elbows resting comfortably on a wing board. Variation in arm position (one arm up) is acceptable if the patient is unable to achieve both arms up. Arm position shall be documented on the treatment planning data sheet. Simulation will be performed using the standard CT protocol at the treating centre, confirmed during the credentialing review. Setup marks will be placed laterally and medially, and tattoos will be applied for future setup at the treatment unit. The preferred method for eliminating patient roll at the time of treatment is to place lateral tattoos on each side of the patient with arms up at the time of simulation. Alternate methods will be confirmed at the time of the credentialing review.

Detailed technical descriptions and figures of CARA are published elsewhere and similar to the completed pilot studies [24–26]. In the experimental arm, CARA settings will be adjusted on a patient-by-patient basis to eliminate the IMF and lateral tissue droop such that that all palpable breast tissue sits anterior to the mid-axilla line. Patient-specific CARA settings will be captured to include in the setup instructions at the treatment unit.

Patients in the control arm will be positioned according to standard practice of care which may include no support, a small foam wedge in the skin fold, a thermoplastic shell, or an alternative supine breast support approved at the time of credentialing review. The method will be recorded with the treatment planning data. No changes to standard practice in the control arm, as reported on the credentialing survey, are permitted during this study without consultation with the steering committee.

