### Data collection

#### Baseline assessment

Data collection activities are shown in Table 1. Patients will have a baseline assessment prior to the first treatment. Patient height and weight, BMI, age, smoking status, RT prescription (including boost), adjuvant chemotherapy, brassiere size (band and cup size), IMF skin fold depth in treatment position, and presence of other skin folds will be recorded. The skin will also be assessed at baseline for any pre-existing conditions such as erythema, telangiectasia, desquamation, or infection. At CT simulation, a baseline photograph of the IMF skin will be acquired as well as a photo of the patient in treatment position. A PRO questionnaire is also collected at baseline.

**Table 1 Tab1:** Schedule of activities and data collection

**Study Activity**	**New patient appointment with radiation oncologist**	**Prior to CT simulation**	**Prior to first treatment**	**Weekly during Breast RT**	**Post-RT weekly to 7 weeks from start of breast RT**
Introduction to study	**X**				
Inclusion/exclusion criteria screening	**X**	**X**			
Informed consent obtained		**X**			
Enrollment and randomization		**X**			
Baseline assessment			**X**		
Patient-reported outcome questionnaire			**X**	**X**	**X**
Skin assessment performed by staff			**X**	**Last week of RT, or for five-day fractionation, last day of RT**	**Optional per patient preference**
Skin dose measurement				**Up to three times per patient; optional for sites other than the coordinating site**	
Timing of clinical flow				**X**	
Standard imaging				**X**	
CBCT imaging				**Up to three times per patient**	
Therapist satisfaction				**Last week of RT, or for five-day fractionation, last day of RT**	

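### The primary model adjusts for skin fold size, but the only fold measurement listed is taken after randomisation in treatment position; unless that means unsupported, the covariate can absorb the device effect

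*Protocol article*

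**What the plan says.** Under Statistical methods – primary outcome, the effect of treatment on moist desquamation in the IMF is estimated by logistic regression, "adjusting for brassiere cup size, skin fold size, BMI, smoking status, and dose fractionation schedule". That section does not say which fold measurement is meant.

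The Baseline assessment section lists the variables collected. The one fold size among them is in this clause: "IMF skin fold depth in treatment position, and presence of other skin folds will be recorded". On timing it says: "Patients will have a baseline assessment prior to the first treatment".

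Randomisation comes earlier. Under Randomization procedure and tracking, the allocation is issued "When an eligible and consenting patient is identified in advance of their CT simulation appointment". Table 1 agrees: enrolment and randomisation are in the column before CT simulation, and the baseline assessment is in the next column, before first treatment.

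For the experimental arm, the CT simulation section says "CARA settings will be adjusted on a patient-by-patient basis to eliminate the IMF and lateral tissue droop", and the last paragraph of the Background says "The IMF is effectively eliminated when using CARA". For controls, the CT simulation section allows no support, a foam wedge in the fold, a thermoplastic shell or another approved support.

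**The concern.** A covariate in the primary model of a randomised trial should not be affected by allocation. Taken at its word, this one is. A patient in the experimental arm is treated on the cradle, so a fold depth recorded in her treatment position is near zero by design. A control patient keeps her fold, perhaps altered by a wedge or shell. Fold depth would then stand in for treatment arm.

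Two harms follow. The standard error of the arm coefficient rises, because arm and covariate carry much the same information. And the coefficient answers a different question: it compares CARA with a control patient extrapolated to zero fold. The sample size section names fewer skin folds as one route to the expected benefit, so this comparison removes benefit that the trial is meant to detect.

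The definition cannot safely wait for an analysis plan. An unsupported depth that was never recorded cannot be recovered later. Eligibility needs only a threshold fold and/or lateral ptosis, and stratification needs only presence of a fold, so neither guarantees that a depth is on file.

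**Working it through.** **Planned sample size.** With 50% versus 30%, two-sided α = 0.05, 80% power and pooled variance:

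n = [1.96·√(2·0.4·0.6) + 0.8416·√(0.25 + 0.21)]² / 0.20² = (1.358 + 0.571)² / 0.04 = 93 per arm.

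This matches the protocol. After 10% loss, 110 × 0.9 = 99 per arm remain, with power 82.4%. No stated figure is in dispute.

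**Inputs.** From the protocol: 50%, 30%, 10% loss, 110 per arm, and fold eliminated with CARA. Assumed, because the protocol gives no depths: unsupported fold depth with mean μ = 2.5 cm and SD σ = 1.5 cm, recorded as 0 in the CARA arm and as the unsupported depth in controls. Let b be the log odds of moist desquamation per cm of fold in controls.

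**Precision.** Without a fold term, SE = √[1/(99·0.25) + 1/(99·0.21)] = √(0.0404 + 0.0481) = 0.30. With depth in treatment position, only controls inform the slope and the arm contrast is extrapolated to depth 0. For b = 0:

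SE = √[0.0481 + 0.0404·(1 + μ²/σ²)] = √[0.0481 + 0.0404·3.78] = 0.45.

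The log odds ratio is ln(0.3/0.7) = −0.847, so power is Φ(0.847/0.448 − 1.96) = 47%. This is the loss when the fold has no prognostic value at all.

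**Absorption.** The arm coefficient becomes about −0.847 + b·μ:
- b = 0.2: −0.847 + 0.5 = −0.347, OR 0.71.
- b = 0.4: −0.847 + 1.0 = +0.153, OR 1.17.
- The sign changes at b = 0.847/2.5 = 0.34 per cm.

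Simulation of this set-up agrees: power 46–48% at b = 0, 11–13% at b = 0.2 and 1–2% at b = 0.4. Adjusting for unsupported depth keeps power at 81–83%.

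**Second depth distribution.** Simulation with 1,500 trials per setting, 99 per arm, depth 0.5 cm + gamma(2,1), with 100% or 80% of patients having a fold (each range runs across those two cases):

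| Share of effect through the fold | Unsupported depth: power, OR | Treatment-position depth: power, OR, SE |
|---|---|---|
| Half | 82–83%, 0.42–0.43 | 16–18%, 0.66, 0.40–0.48 |
| All | 81–82%, 0.43 | 2–3%, 1.01, 0.42–0.50 |
| None, but unsupported depth prognostic in both arms (0.4 per cm) | 84–86%, 0.39–0.40 | 1–3%, 0.95–1.19, 0.42–0.51 |

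Without any fold term, power is 81–84%. Patients without a fold soften the loss. If 20% have none, μ = 2.0 cm and σ² = 0.8·(2 + 6.25) − 4 = 2.6. With b = 0 this gives SE = √[0.0481 + 0.0404·(1 + 4/2.6)] = 0.39 and power of about 59%.

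**The case against.** The strongest reply is that the literal reading is not the intended one. The last paragraph of the Background defines the IMF by the skin in contact when the breast is unsupported and supine, so an IMF fold depth could be an unsupported depth by definition. The Inclusion criteria apply the term treatment position to a breast without support, so the phrase may mean only supine on the angled board. Fold depth is listed with patient characteristics such as BMI and cup size, and a value that is zero by design in one arm would be useless among them. No passage says that depth is measured with CARA in place. Measuring after allocation does no harm in itself if the breast is unsupported.

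All of this stands, and it rules out the stronger claim that a reader might infer: that the primary model will absorb the device effect. It does not settle the matter. The Inclusion criteria state the unsupported condition expressly, and the Baseline assessment section omits it. The same paragraph calls for a photograph in treatment position at CT simulation, which in the experimental arm would naturally show the CARA set-up. Centres could read the phrase differently.

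Three further limits are fair:
- Control depth in treatment position need not be the unsupported depth, because wedges and shells are allowed, and some patients qualify on lateral ptosis alone. Both weaken the collinearity assumed above.
- A reversed odds ratio is not something that the protocol implies. It needs a slope above about 0.34 per cm at a mean depth of 2.5 cm. If the slope acts through the fold, that means harm by other routes, whereas the sample size section expects a second benefit through V105% and breast separation. Otherwise unsupported depth must strongly mark risk in both arms.
- The unadjusted chi-square or Fisher test is planned and does not use the covariate. It is named as an additional comparison, however, and the article does not say which result governs if the two disagree.

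**Conclusion.** The point holds as an ambiguity with serious consequences. The protocol fixes a measurement state and a time for the only fold size it lists, and on the plain reading these make a primary-model covariate depend on allocation. On the other reading there is no bias and power stays at 81–86%.

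Under the literal reading and the assumed depths, the standard error of the log odds ratio rises from about 0.30 to 0.40–0.51. Power falls from about 82% to under 50% when every patient has a fold (about 59% if a fifth have none and the fold is not prognostic), and to under 20% when half or more of the effect runs through the fold. These sizes are illustrative. The presence of the problem under that reading follows from the design and does not depend on the assumed depths.

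**What to change.** State in both Baseline assessment and Statistical methods – primary outcome that the covariate is IMF fold depth with the breast unsupported, patient supine on the board, recorded at eligibility screening before allocation. Bring Table 1 into line. Keep any depth measured in the supported treatment set-up as a descriptive variable outside the primary model.

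The cost is one sentence and one form field, because the unsupported breast is already examined for eligibility and for the fold-presence stratum. For patients already enrolled, establish without reference to outcome how depth was taken. Where no unsupported depth exists, fold presence at randomisation is an available covariate that allocation cannot have changed.

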### Participant withdrawal

A participant may withdraw from the study for any reason at any time. Patients may also be withdrawn from the study at the discretion of the investigator and/or treatment team, for example, if problems arise with healing of the surgical wound if this interferes with the required skin assessments or causes treatment interruption or delay. Participants withdrawn from the study shall continue to receive appropriate treatment as decided upon with their radiation oncologist. Data collected up to the point of withdrawal will remain in the study.

Patients in the control arm who withdraw from the study post-CT simulation will continue with treatment as planned, with no interruption. Patients in the experimental study arm who withdraw from the study will decide, in discussion with the treating oncologist, whether to continue with CARA or to change to the standard of care breast positioning method. In the latter case, the patient will be required to undergo repeat CT simulation and planning with the standard method. This process typically requires one week and may be done currently with continued treatment with CARA if desired. Otherwise, a treatment interruption may be required.

A participant is considered to have completed the study if they have completed all phases of the study including treatment and the final PRO questionnaire. If a participant fails to complete a follow-up PRO assessment, the site will attempt to contact the participant weekly and counsel the participant on the importance of maintaining the assigned follow-up schedule and ascertain whether the participant wishes to and/or should continue in the study. Should the participant remain unreachable out to eight weeks from the start of RT, they will be considered to have withdrawn from the study.

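### The primary analysis keeps incomplete patients who reported moist desquamation and drops those who did not, so unequal completeness between the open-label arms can bias the odds ratio in either direction

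*Protocol article*

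**What the plan says.** The rule is in the protocol article under Statistical methods – primary outcome and has three parts:

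- Incomplete with MD: "Those participants who do not complete all follow-up but have reported MD are included in the analysis".
- Incomplete without reported MD: "Those who do not complete all follow-up and do not report MD will be excluded from the primary analysis".
- Fallback: "A sensitivity analysis including those lost to follow-up will be done using multiple imputations for missing data".

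Other sections bear on how the rule would work:

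- Staff skin assessments: positioning is open label to patients and treating staff.
- Primary endpoint and measures: MD is scored from the patient's own questionnaire unless a blinded assessor rules it out.
- Participant withdrawal: completion means finishing all study phases, including treatment and the last patient-reported outcome (PRO) questionnaire. The options on withdrawal differ by arm.
- Sample size calculation and recruitment period: the only loss figure is 10%, from the pilot study, with no split by arm.

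**The concern.** Under this rule an incomplete patient can enter the primary analysis only as an event. Those removed are not known non-events. They are patients with no MD reported by the time contact ended, and some may have developed it later.

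If dropout were unrelated to MD, a completers-only analysis would leave the OR unbiased however unequal the losses. The rule removes that protection. It adds the early-reported events of incomplete patients to the numerator and leaves their event-free counterparts out of the denominator. The arm that loses more patients then appears to have more MD.

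Unequal completeness is plausible because patients know their arm, report the endpoint themselves, and face different choices on withdrawal. At stake are the main effect estimate, its p-value, and the MD incidence reported for each arm.

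**Working it through.** **The plan's own figure.** Inputs, from the sample size section: "we expect a control arm rate of 50% for any degree of MD in the IMF", "we hypothesize a rate of 30% moist desquamation in the study arm", "with 80% power and two-tailed α = 0.05". With pooled variance, n = [1.96·√(2·0.40·0.60) + 0.8416·√(0.25 + 0.21)]² / 0.20² = 93.0, which matches "the sample size is 93 patients in each arm". Allowing for 10% loss, 93/0.90 = 103.3, so 104. Enrolling 110 leaves 99 evaluable and 82.4% power. The sample size is sound and is not in dispute.

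**Model of the rule.** In each arm let p be the true MD rate, d the share of patients incomplete, and f the share of incomplete MD patients who reported MD before stopping. Take incompleteness as independent of MD. Values of d by arm and of f are assumptions.

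- Analysed events per randomised patient: p·[(1−d) + d·f]
- Analysed non-events: (1−p)·(1−d)
- Analysed odds = true odds × [1 + d·f/(1−d)]
- At f = 1, analysed OR = true OR × (1−d_control)/(1−d_CARA)
- At f = 0 the rule reduces to completers only and adds no bias.

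**Equal loss, 10% in each arm, f = 1.** A true 50% reads as 0.50/(0.50 + 0.45) = 52.6%. A true 30% reads as 0.30/(0.30 + 0.63) = 32.3%. The OR is unchanged at 0.429.

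**Unequal loss.** Type I error and power come from simulated trials with 110 per arm and the unadjusted Pearson chi-square test.

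| True MD (control / CARA) | Incomplete (control / CARA) | f | Analysed rates | OR | Rejection rate |
|---|---|---|---|---|---|
| 50% / 50% | 15% / 5% | 1 | 54.1% / 51.3% | 0.85/0.95 = 0.89 | about 6.9% |
| 50% / 50% | 15% / 5% | 0.5 | 52.1% / 50.6% | 1.0263/1.0882 = 0.94 | about 5.5% |
| 50% / 50% | 5% / 15% | 1 | 51.3% / 54.1% | 0.95/0.85 = 1.12 | about 6.9% |
| 40% / 40% | 20% / 5% | 1 | 45.5% / 41.2% | 0.80/0.95 = 0.84 | about 9.4% |
| 40% / 40% | 20% / 5% | 0.5 | 42.9% / 40.6% | 0.91 | about 6.3% |
| 50% / 30% | 15% / 5% | 1 | 54.1% / 31.1% | 0.429 × 0.85/0.95 = 0.383 | about 92% (power) |
| 50% / 30% | 5% / 15% | 1 | 51.3% / 33.5% | 0.429 × 0.95/0.85 = 0.479 | about 74% (power) |

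For the last row, a completers-only analysis with the same losses has about 82% power. The rule itself costs about 8 points there.

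**Which patients count as incomplete.** If the rule is read as requiring every weekly form, one missed form removes a patient without MD. At an assumed 5% miss rate per form, the share missing at least one is 1 − 0.95⁷ = 30% for seven forms, 1 − 0.95⁴ = 18.5% for four, and 1 − 0.95³ = 14% for three. The number of forms depends on the schedule: Table 1 has weekly forms throughout, while Patient population starts them in the last week of treatment. These shares are upper bounds, because they ignore the staff follow-up of missed forms that the article describes.

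**The case against.** The strongest case against the point is about size. The only documented loss is 10%. If losses average that with a 10-point gap between arms, the OR shifts by about 11% to 12% at f = 1 and by about half that at f = 0.5. With equal completeness the OR is not biased at all. The planned multiple imputation would also expose a material discrepancy. All of this stands and limits the severity. It does not remove the problem, because the main estimate and p-value still come from a set selected by outcome.

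A reader might also draw stronger conclusions that the documents do not support:

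- **That the rule favours the device.** Nothing indicates which arm will lose more patients, and the reverse split works against CARA.
- **That unblinded staff could remove patients with skin reactions.** The article does say "Patients may also be withdrawn from the study at the discretion of the investigator and/or treatment team", but its example is surgical-wound healing that disrupts assessments or treatment, and data up to withdrawal are kept.
- **That the wound-dressing exclusion removes patients after randomisation.** It is an eligibility criterion, screened before CT simulation, and no passage takes later users out of the analysis.
- **That imputation is unbiased.** It needs missing-at-random and an adequate model. Dropout linked to unreported MD would breach the first.

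**Conclusion.** The point holds as a flaw in a stated rule for the primary endpoint, not as missing detail. Whenever f exceeds zero, incidence is overstated in both arms, and any gap in completeness between arms biases the OR, in a direction that cannot be predicted.

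Near the documented 10% loss, with an assumed 15% versus 5% split, the bias is modest: 1.5 to 3 percentage points under the null and type I error of about 5.5% to 6.9%. It grows with wider gaps or a strict reading of completion. These figures assume incompleteness independent of MD and use the unadjusted test, not the adjusted logistic regression planned as the main model. Rating: should be fixed.

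**What to change.** 1. Make the primary analysis all randomised patients by assigned arm, using the multiple imputation already planned. Impute from the observed weekly PROs, arm, stratification factors and baseline covariates, and state the missing-at-random assumption.
2. Move the present inclusion rule to a sensitivity analysis.
3. Align the wording on completing follow-up with the definition under Participant withdrawal, so that an intermittently missed form does not remove a patient.

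The cost is a change of wording in the protocol and analysis plan, with no new visits and no change in sample size. The downside is that the primary result then relies on an imputation model, which has to be specified before the data are seen.
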